### Assessments

Regular visits are planned at baseline and every 3 months thereafter up to month 18. When a flare occurs, patients are seen within two days, but at least within a week, and additionally an extra visit is planned after 4 weeks. In Additional file 1: Table S1 we outlined all the visits and assessments.

### Randomisation, allocation concealment and blinding

Allocation is stratified for adalimumab and etanercept using stratified block randomization in random sized blocks and a ratio of 2:1. Patients will be randomised by the research physician using a computer-generated randomisation list, which has been transferred to paper sheets and put in sealed envelopes.

This study uses a controlled and randomised, but only partly blinded design, as patients and physicians are not blinded for allocation. Blinding of the assessor performing the joint scores was strived for, and this was done by instructing both patients and the independent joint assessor to first score the DAS28CRP, before assessing medication changes and adverse effects.

Although triple blinding (patients, physicians, researcher) would methodologically be preferable, this is unfeasible because dose reduction in this study is done via increasing the interval instead of decreasing the dosage per injection. The latter would not be sensible, since TNF blockers are given using prefilled injection pens. Blinding of patient and physician is possible when using interval widening, but would be very difficult. The unblinded nature of the study could result in information and attribution bias, as flares in patients in whom the dose is reduced would possible be reported sooner because they would be attributed to the intervention. This bias can however fortunately only lead to overestimation of the drawbacks of a dose reduction strategy, not underestimation, and therefore the higher risk of bias was accepted.

### Sample size

The null hypothesis in this study is that the intervention is inferior compared to the control arm by more than the non-inferiority margin δ (H0: μ1-μ2 > δ). The alternative hypothesis rejects this null hypothesis (H1: μ1-μ2 ≤ δ), thus proving non-inferiority. The sample size calculation is motivated as follows [42] using the fomula as shown.

$$n_{1}=kn_{2}$$

$$n_{2}=\frac{{\left(Z_{a}+Z_{\beta }\right)}^{2}}{{\left(\epsilon -\delta \right)}^{2}}\left[\frac{p_{1}\left(1-p_{1}\right)}{k}+p_{2}\left(1-p_{2}\right)\right]$$

We estimated that 20% (p_1_ = 0.80) of patients will experience the primary outcome in the usual care arm (persistent flare), with an estimated 15% (p_2_ = 0.85) of patients with this outcome in the intervention arm. Applying one sided testing, an alpha of 0.05 (Z_α_ = 1.64, non-inferiority testing one sided), power 1-beta 0.8 (Z_β_ = 0.84), an inferiority margin of 20% (δ = -0.2), and randomisation ratio of 2:1 intervention versus control (k = 2) resulted in n = 114 and n = 57 for intervention and control arm. Accounting for a 10% drop-out, we choose to include 180 patients in total.

The estimation of proportion of primary outcome in both groups and magnitude of the non-inferiority margin (δ) are motivated as follows. Although clear data are absent, based on the few dose reduction studies that included a control group, and on previously published drug survival curves for adalimumab and etanercept in our population, we estimated that after 18 month in the usual care group 15% of patients would have changed their biologic therapy due to insufficient disease control [12,15,16,28]. We furthermore assumed that 15% of patients in the intervention group can ultimately stop the drug (without persistent flare), resulting in cumulative incidence of 85% flares in the group of patients with partial dose decrease. Of these patients, we estimate that 5% will not respond to reinstallment of the TNF blocker and experience a persistent flare. Thus, we expect a cumulative incidence of persistent flare of 15 + 5 = 20% in the intervention arm.

A difference in persistent flare of over 20% between usual care and dose reduction would constitute a clinical relevant non-inferiority margin in our opinion. The underlying reasoning is, that it is to be expected that half of the patients who start another biologic for a flare will show response again within three months (21–23). Half of 20% of the patients would therefore experience a persistent flare, a more prolonged period with uncontrolled disease activity, resulting in a NNH of 10. In our clinical view, this seems to balance nicely with an expected chance of being able to reduce the dose or stop the drug of approximately 60 and 15% respectively (NNT 1.5 and 6 respectively), as much more patients are expected to benefit than to be harmed using this non-inferiority margin. The ratio of 2:1 for intervention and control sample size is chosen to be able to include more determinants in a prediction model for successful dose reduction.

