We have chosen to operationalise low disease activity state by either a DAS28CRP < 3.2 or judgment of low disease activity by the rheumatologist at two subsequent visits at least 3 month apart. This means also patients with a DAS28 ≥ 3.2, but judged to have a low disease activity by their treating rheumatologist, are eligible for inclusion. This is firstly because several biologic registries show that mean DAS28 in TNF Blocker treated patients in clinical practice is around 3.2 [28]. This means that over 50% of the patients has a DAS28 ≥ 3.2, and even more are not in remission, but that both the patient and rheumatologist judge the disease activity to be low enough not to warrant switch of treatment. Limiting inclusion to only patients with DAS28 < 3.2 or even < 2.6 would therefore limit generalisability to current treatment practices. It might be rebutted that these higher disease activity scores reflect undertreatment and thus result in suboptimalisation. A DAS28 can however be inflated by OA associated joint pain, concomitant fibromyalgia or spuriously elevated ESR. This is also the rationale for use of DAS28CRP instead of DAS28 ESR. Another important consideration is that we treat RA patients for two reasons: firstly to improve current signs and symptoms, and secondly to prevent joint damage. With respect to the first reason, it is important to note that the patient acceptable symptom state of the DAS28, has been found to be around 3.5 to 3.9, clearly higher than the currently advocated treatment aims of 2.6 or 3.2 [29]. For prevention of joint damage it is important to realize that not all patients have high risk of erosive disease and a need for prognosis modification [30]. Therefore, accepting somewhat higher disease activity can be legitimate and is indeed part of clinical practice. Of note, per October 19, 2012, all patients (n = 180) have been enrolled and randomised. Mean DAS28CRP is 2.2, and 8% of patients had a DAS28 > 3.2.

Because we aimed for maximal generalisability, we chose to only exclude patients if they have co morbidity which also requires treatment with anti-TNF and thus prevents dose reduction (e.g. Crohns disease), or when it is to be expected that the outcome cannot be measured (short life expectancy, planned major surgery).

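### The 180 patients allow for 5% drop-out, not the stated 10%: 171 evaluable patients would need 190, and at 10% loss power by the plan's formula is 78%, not 80%

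*Protocol article*

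**What the plan says.** All the figures are in the protocol article. The Sample size section uses a normal-approximation formula for non-inferiority of two proportions with 2:1 allocation (k = 2). It sets a one-sided alpha of 0.05 with Z = 1.64, "power 1-beta 0.8 (Z_β_ = 0.84"), and "an inferiority margin of 20% (δ = -0.2"). With the proportions free of persistent flare set at 0.80 and 0.85, the calculation "resulted in n = 114 and n = 57 for intervention and control arm", which is 171 patients in total.

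The next sentence makes the allowance for loss: "Accounting for a 10% drop-out, we choose to include 180 patients in total". The article gives no other inflation rule. The section on patients, eligibility and generalisability confirms that recruitment ended at that number: "all patients (n = 180) have been enrolled and randomised".

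**The concern.** The last two figures of the calculation do not fit together. Going from 171 to 180 adds nine patients, which is 5.3% of 171, while the sentence says that 10% loss is covered. On neither of the usual inflation rules does 10% turn 171 into 180.

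What is at stake is the power claimed for the primary comparison. A reader would take it that the trial can lose one patient in ten and keep 80% power to show non-inferiority, when its margin for loss is half of that. The point matters more for the per-protocol analysis. The Planned data analysis section adds that analysis as a guard against a falsely positive non-inferiority result, and such a set usually loses protocol deviators as well as drop-outs.

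**Working it through.** **Inputs** (all from the Sample size section): Zα = 1.64, Zβ = 0.84, δ = −0.20, k = 2, p₁ = 0.80, p₂ = 0.85, drop-out 10%, total 180. In the formula, p₁ belongs to the larger arm (n₁ = k·n₂), which is the intervention arm. So ε = p₁ − p₂ = −0.05 and ε − δ = 0.15.

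**Step 1: reproduce the evaluable number.**

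n₂ = (1.64 + 0.84)² / 0.15² × [0.80 × 0.20 / 2 + 0.85 × 0.15] = 6.1504 / 0.0225 × 0.2075 = 56.7, rounded up to 57.

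n₁ = 2 × 57 = 114, and the total is 171. This agrees with the article.

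**Step 2: apply the drop-out allowance.**

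| Rule | Calculation | Total |
|---|---|---|
| N/(1 − d), d = 10% | 171/0.90 | 190 |
| N × (1 + d), d = 10% | 171 × 1.10 = 188.1 | 189 |
| N/(1 − d), d = 5% | 171/0.95 | 180 |

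In the other direction, 180 × 0.90 = 162, which is 9 below 171, and 1 − 171/180 = 5.0%. The stated total is therefore the 5% figure, and it is 10 short of the 10% figure (10/190 = 5%).

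**Step 3: power by the same formula.**

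Power = Φ(0.15/SE − 1.645), where SE = √(0.16/n₁ + 0.1275/n₂).

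For 108:54, SE = √(0.16/108 + 0.1275/54) = 0.0620, and Φ(0.15/0.0620 − 1.645) = 0.781.

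| Loss from 180 | Evaluable (intervention:control) | Power |
|---|---|---|
| 0% | 180 (120:60) | 81.7% |
| 5% | 171 (114:57) | 80.0% |
| 10% | 162 (108:54) | 78.1% |
| 15% | 153 (102:51) | 76.0% |
| 20% | 144 (96:48) | 73.8% |

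The 15% and 20% rows are assumed exclusion rates, chosen to show what a per-protocol set might face. The article gives no such rate.

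**Step 4: which arm has which rate.** The section first puts 20% in usual care and 15% in the intervention arm: its words for the former are "We estimated that 20% (p_1_ = 0.80) of patients will experience the primary outcome in the usual care arm (persistent flare". Further on, when it motivates the rates, it puts 15% in usual care and 20% in the intervention arm. Only the second assignment reproduces 171; with the first, the same formula asks for about 23 controls. The power figures above therefore use 20% in the intervention arm. The drop-out arithmetic in Step 2 does not depend on this choice.

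**The case against.** The arithmetic in Step 2 is hard to dispute. The case on the other side is that it hardly matters, and it has four parts.

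- **The power loss is within the error of the approximation.** Exact binomial enumeration with a one-sided 5% Wald limit gives 80.1% at 108:54. This stands: the 78.1% is a result of the planning formula, and actual power at 10% loss may be close to 80%. But the same enumeration gives 81.7% at 114:57, so the shortfall against the planned number remains, at 1.6 points. The article planned by its formula, and it is by that formula that its claim fails.
- **Drop-outs may still count in the intention-to-treat analysis.** Multiple imputation is planned if its assumptions hold, and a patient who leaves after a persistent flare has already contributed the endpoint. With all 180 analysed, formula power is 81.7%. This limits the consequence. It does not rescue the sentence, since the authors chose to inflate for drop-out and named the rate. Nor does imputation restore all the lost information, or return patients excluded from the per-protocol set.
- **The per-protocol figures rest on assumed exclusion rates, and the article claims no power for that set.** This stands. Those figures are illustrative, and reporting them is optional.
- **The planning rates are rough, and enrolment is closed.** Both are true. They argue for correcting the text and against any change to the trial.

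**Conclusion.** The concern holds. The total of 180 does not follow from 171 evaluable patients and 10% drop-out; it corresponds to 5%. The required total was 190, so the trial is 10 patients short of its own specification. At 10% loss, power by the article's formula is 78.1% instead of 80%.

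The power figure assumes persistent flare in 20% of the intervention arm and 15% of the control arm, a margin of 20 percentage points, a one-sided 5% test, equal proportional loss in both arms, and that patients who drop out contribute nothing to the analysis. Under exact calculation or with imputation the practical loss is smaller still. This is a definite error in the statement supporting the primary analysis, with a modest effect and no threat to the validity of the trial.

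**What to change.** Replace the drop-out sentence with one that matches the numbers, for example: *With 180 patients randomised, power is 80% with up to 5% drop-out (171 evaluable) and about 78% with 10% drop-out (162 evaluable), assuming persistent flare in 20% of the intervention arm and 15% of the usual care arm.* Naming the arms in that sentence also makes clear which rates the calculation used.

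It would help to give the power of the per-protocol analysis at a stated exclusion rate, here or in the statistical analysis plan, but the correction does not depend on it.

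The cost is one sentence and a slightly less favourable power statement. No patients are added, and neither the conduct of the trial nor its analysis changes.

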### Objectives

The aim of the study is to test whether a tight control strategy with protocollised dose reduction and discontinuation in RA patients using TNF blockers is non-inferior with regard to disease control compared to a strategy without dose reduction attempt, and superior with regard to cost effectiveness. This translates in the following research questions:

#### **
*Primary objective*
**

– To assess whether the difference in cumulative incidence in persistent RA flares with a duration > 3 months between the intervention group and the usual care group of RA patients does not exceed the non-inferiority margin of 20% after 18 months of follow up.

#### **
*Secondary objectives*
**

– To compare the cumulative incidence of patients fulfilling flare criteria in the intervention and the usual care group after 9 months and after 18 months of follow up.

– lTo compare the cumulative incidence of patients with persistent RA flare resulting in change of biological between the intervention and the usual care group after 9 months and after 18 months of follow up.

– To compare the proportion of patients with a DAS28 < 3.2, DAS28 < 2.6 and fulfilling remission criteria according to ACR/EULAR criteria between the intervention and usual care group at 9 and 18 months follow up.

– To compare the mean DAS28 and the mean time averaged DAS28 between the intervention and usual care group at 9 and 18 months follow up.

– To compare the proportion of patients using NSAIDs, glucocorticoids or DMARDs between the intervention and usual care group at 9 and 18 months follow up.

– To compare the mean Health assessment questionnaire disability index (HAQ-DI) between intervention and usual care group at 9 and 18 months follow-up.

– To compare the proportion of patients with a change in modified Sharp-van der Heijde Score exceeding the minimal clinical important change (MCIC) between the intervention and usual care group at 18 months.

– To compare the proportion of patients developing adverse events with special attention for allergic/injection reactions between the intervention and usual care group.

– To estimate the decremental cost effectiveness ratio of a protocollised dose reduction/withdrawal strategy of adalimumab or etanercept compared to usual care for the 9 months induction phase and for the 12 months maintenance phase.

#### **
*Study design rationale*
**

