The comparison made in this study is between usual care and an alternative strategy (dose reduction) that aims to preserve, but not improve, disease control, whilst minimising the amount of TNF blocker. Therefore, a non-inferiority design (“can we achieve the same effect with less effort”) instead of the classic superiority RCT design (“can we do better with more effort”) was chosen. Of note, this is an adaptation of the original registered research protocol.

#### **
*Study outcome rationale*
**

As disease control is the domain that should remain non-inferior, an outcome measure of disease control had to be selected as primary outcome. Several options come to mind, each with specific advantages and drawbacks.

A straightforward option would be a comparison of disease activity at study end, like for example mean DAS28 with non-inferiority margin of 0.3 DAS28 points. However, it can be expected that at study end no difference is found between the two strategies because patients are treat-to-target, but that flaring is much more frequent during the study in the dose reduction arm. Comparison of time integrated DAS28 might be therefore a better alternative, with the bonus of lower sample size requirements due to the repeated measurements [18]. However, disease activity AUC values are harder to interpret and less informative for a practising clinician than percentage of patients with a flare. The latter also facilitates the calculation of numbers needed to treat/harm (NNT/NNH), thus making results easier to interpret and communicate to patients and physicians alike.

Another option would therefore be to use cumulative incidence of flares as primary outcome, and this is chosen in the majority of dose reduction and discontinuation studies. However, temporary flares that improve after reinstallment of therapy and without a large impact on overall disease control will inevitably occur more frequent in a dose reduction arm, but are clinically less relevant than persisting flares. We therefore chose to assess non-inferiority with respect to cumulative incidence of persisting flare, which is defined as a flare according to the DAS28 based OMERACT validated flare criterion persisting for at least 3 months (independent of treatment changes).

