### Outcome measures

The outcome measures used in this study include disease activity (DAS28CRP based RA Flare criterion, mean and time integrated DAS28CRP), function (HAQ DI), radiological damage (Modified Sharp van der Heijde score, MSvdH), Adverse events (CTC 4.0 criteria), utility (Euroqol 5D 5 L) and costs [33-39].

#### **
*Definition of flare*
**

RA Flare in this study is defined in both treatment arms as a DAS28 increase compared to baseline of more than 1.2 or a DAS28 increase of more than 0.6 with a current DAS28 ≥ 3.2 at two separate timepoints at least 4 weeks apart. This criterion has been validated recently, and has been shown to have the optimal tradeoff between sensitivity and specificity, and the best construct and criterion validity [40]. As it has been shown that flares are frequently temporary and occur and disappear without regimen change, a flare is only considered a flare if it is confirmed after at least 4 weeks [11]. Patients are however not left untreated, and when a flare in disease activity occurs, all bridging therapy including i.a. or im steroids or NSAID can be given and are allowed. Of note, flares are defined with change compared to baseline, not compared to the last visit, to prevent undertreatment in patients with a slight increase in disease in subsequent visits.

When the flare is confirmed after 4 weeks, in both treatment arms patients receive optimal treatment for the flare, for example protocollised reinstallment or dose increase of the TNF blocker or change to another biologic or DMARD. Only patients in whom the flare persist longer than three months (in spite of all treatment intensivation) are classified as having persistent flare, the primary outcome of this study.

#### **
*Secondary outcomes*
**

##### 

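### The 80% power rests on a 15% rate of changing biologic used as the persistent-flare rate, and the margin's justification links switching and persistent flare differently

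*Protocol article*

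**What the plan says.** All references are to the protocol article.

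- **Endpoint.** Outcome measures, Definition of flare: "Only patients in whom the flare persist longer than three months (in spite of all treatment intensivation) are classified as having persistent flare". The outcome rationale under Objectives describes the chosen outcome as a flare "persisting for at least 3 months (independent of treatment changes".
- **A separate switching outcome.** The secondary objectives list "persistent RA flare resulting in change of biological between the intervention and the usual care group" as its own comparison.
- **Control rate.** Sample size derives it from controlled dose-reduction studies and local drug survival curves: "in the usual care group 15% of patients would have changed their biologic therapy due to insufficient disease control".
- **Intervention rate.** A further 5% are expected not to respond when the TNF blocker is reinstated. "Thus, we expect a cumulative incidence of persistent flare of 15 + 5 = 20% in the intervention arm".
- **Arm labels.** The parameter sentence earlier in the same section assigns 20% to usual care and 15% to the intervention, the reverse of this derivation.
- **Margin.** The next paragraph calls 20% a difference in persistent flare. It then reasons that "half of the patients who start another biologic for a flare will show response again within three months", so that half of the 20% would have persistent flare, giving an NNH of 10.

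**The concern.** The 15% counts patients who changed drug. The primary endpoint counts patients whose flare lasted more than three months. The plan keeps these apart in its definitions and objectives, yet the sample size uses the first as the second and then adds a true persistent-flare figure to it, so 15 + 5 sums two different events. One paragraph later, switching and persistent flare are no longer treated as equal: only half of the switchers have the endpoint.

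Two stated figures depend on this. The power is valid only at the event rates assumed for the endpoint actually analysed. The clinical argument for the margin weighs an NNH of 10 against the expected benefits of tapering, but the primary objective places the full 20 points on persistent flare.

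**Working it through.** **1. Inputs (Sample size).** One-sided alpha 0.05 (z = 1.64), power 0.80 (z = 0.84), margin 0.20, allocation 2:1, and persistent flare at 15% and 20%.

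**2. Reproducing the plan's figure.** With control success 0.85 and intervention success 0.80:

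n(control) = (1.64 + 0.84)² / (0.20 − 0.05)² × [0.80 × 0.20 / 2 + 0.85 × 0.15] = 6.1504 / 0.0225 × 0.2075 = 56.7

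This gives 57 control and 114 intervention patients, as stated.

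**3. Which arm has which rate.** Taking the parameter sentence literally (control 20%, intervention 15%) gives 6.1504 / 0.0625 × [0.85 × 0.15 / 2 + 0.80 × 0.20] = 22.0, so about 22 and 44. The stated 57 and 114 therefore need control 15% and intervention 20%, which agrees with the later derivation.

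**4. Power at other persistent-flare rates.** Sample sizes (57 and 114) and margin (0.20) are held fixed, with

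SE = √[pI(1 − pI)/114 + pC(1 − pC)/57]

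Power = Φ((0.20 − (pI − pC))/SE − 1.645)

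| Control | Intervention | SE | Power | Status of the rates |
|---|---|---|---|---|
| 7.5% | 10% | 0.0448 | 99% | both planned rates halved (inference) |
| 7.5% | 12.5% | 0.0467 | 94% | 15% halved, 5% added (inference) |
| 15% | 20% | 0.0603 | 80% | as planned |
| 20% | 25% | 0.0667 | 73% | assumed |
| 25% | 30% | 0.0716 | 67% | assumed |

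The first two rows apply the margin paragraph's halving to the 15%, which the plan does not do. The last two assume that persistent flares without a change of biologic raise both rates and that the 5-point difference stays. With 54 and 108 evaluable patients (180 less 10%), each power is lower by at most about 2 percentage points.

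**5. The margin.** The primary objective allows a difference of 20 points in persistent flare: NNH = 1/0.20 = 5. The margin paragraph takes half of 20%, which is 10%: NNH = 1/0.10 = 10. Both cannot describe the same margin on the same endpoint.

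**The case against.** The plan says that clear data are absent and names its proxies, so the 15% is a disclosed assumption, and the arithmetic from it is correct. Whether the cited sources support 15% for persistent flare cannot be checked here. All of this stands, but the section labels the figure persistent flare without saying how a switching rate becomes one.

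Three stronger readings are tempting, and the documents do not support them.

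- **That the plan's own control rate is 7.5%.** The plan halves only the 20% margin. A patient who responds within three months of starting another biologic may still meet the endpoint, because the flare has already lasted the four or more weeks needed for confirmation. The secondary objective's wording, "persistent RA flare resulting in change of biological", presents the switch as a consequence of persistent flare, which would make most switchers endpoint cases. Persistent flares managed without a switch would add to them. So 15% could be too high or too low. The statement that 20 points would allow a rise to about 3.7 times control (27.5/7.5) falls with the 7.5%.
- **That the trial is underpowered.** The illustrative range brackets 80%, and the scenarios below 80% have no source in the plan. If the halving is applied, power rises.
- **That the result should also be judged against a tighter, power-derived bound.** That bound would rest on an unestablished rate. The plan justifies its margin clinically, and the observed confidence limit will show what the data exclude.

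It is also fair to say that all 180 patients were already randomised, so the correction cannot change the sample. It can still correct what the article states.

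**Conclusion.** The point holds as an inconsistency between endpoints, not as a calculation error. The 80% power is right if the persistent-flare rates are 15% and 20%, but the derivation gives a switching rate for the first and a sum of two different events for the second. The margin paragraph links switching to persistent flare differently again, so the quoted NNH of 10 does not belong to a 20-point margin on persistent flare; that NNH is 5.

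The effect on power is uncertain in direction: about 67% to 99% over the scenarios shown, all of them inferred or assumed except the planned one. The calculations use the plan's normal approximation, its one-sided 5% level and 57 and 114 evaluable patients.

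**What to change.** In the Sample size section:

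1. Put the event-rate paragraph and the margin paragraph on one endpoint, persistent flare as defined, and state what share of switchers is taken to have it.
2. Give the expected persistent-flare rate in each arm as a range, and make the arm labels in the parameter sentence agree with the derivation.
3. Restate the power of the enrolled sample across that range for the 20-point margin.
4. Correct the NNH implied by a 20-point margin on persistent flare, and reconcile the clinical justification with it.

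This is rewording and a short recalculation. Enrolment, endpoint and margin stay as they are, and no second bound is added. The small cost is that the stated power becomes a range.

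### The 20-point margin on persistent flare is defended with an NNH of 10, but on the endpoint as defined it tolerates an NNH of 5

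*Protocol article*

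**What the plan says.** The primary objective (Objectives) is that the difference in cumulative incidence of persistent flare "does not exceed the non-inferiority margin of 20% after 18 months of follow up". The margin paragraph under Sample size uses the same outcome: "A difference in persistent flare of over 20% between usual care and dose reduction would constitute a clinical relevant non-inferiority margin".

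Outcome measures (Definition of flare) fixes what counts: "Only patients in whom the flare persist longer than three months (in spite of all treatment intensivation) are classified as having persistent flare". Treatment after a confirmed flare may be "protocollised reinstallment or dose increase of the TNF blocker or change to another biologic or DMARD". The outcome rationale under Objectives adds that persistence is judged whatever treatment changes are made.

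The margin paragraph then supposes that half of those who start another biologic will respond within three months and concludes: "Half of 20% of the patients would therefore experience a persistent flare". It reports this as an NNH of 10 and weighs it against expected chances of about 60% for dose reduction and 15% for stopping, given as "NNT 1.5 and 6 respectively".

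Earlier in the same section, the usual-care rate is derived from an estimate that "15% of patients would have changed their biologic therapy due to insufficient disease control".

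**The concern.** The margin paragraph gives one outcome two sizes at the same margin: a 20-point difference in persistent flare, and then half of that as the patients who have a persistent flare. The discount is for response to a new biologic, which fits a count of flares leading to a switch. The primary endpoint is a different count, taken after, or regardless of, treatment changes that include such a switch.

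This paragraph is the only justification the article gives for the primary decision threshold, and it turns on a harm-benefit balance. If harm at the margin is understated by a factor of two, a result that only just meets 20 points could be read as having excluded a 1-in-10 harm when it has excluded a 1-in-5 harm.

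**Working it through.** **Inputs.** Margin 20 points on persistent flare (Objectives; Sample size). Discount 0.5, stated NNH 10, expected benefits 60% and 15% (Sample size, margin paragraph). Planning rates 15% usual care and 20% intervention (Sample size, derivation paragraph; the paragraph with the formula attaches these two rates to the opposite arms, and the derivation is followed here). Z values 1.64 and 0.84, δ = -0.2, k = 2 (Sample size).

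**1. The stated NNH.** NNH = 1/risk difference. 1/(0.5 × 0.20) = 1/0.10 = 10. The printed figure is reached only with the halving.

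**2. Which margin the sample size uses.** On the flare-free scale p1 = 0.80 (intervention) and p2 = 0.85 (control), so ε = -0.05 and ε - δ = 0.15.

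n2 = (1.64 + 0.84)² / 0.15² × [0.80 × 0.20/2 + 0.85 × 0.15] = 6.1504/0.0225 × 0.2075 = 56.7; n1 = 2 × 56.7 = 113.4.

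Rounded up, these are the stated 57 and 114. The full 20 points, unhalved, is applied to persistent flare.

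**3. NNH at the margin on the endpoint tested.** 1/0.20 = 5. With 15% in usual care, the null boundary is 15% + 20% = 35% in the intervention arm.

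**4. The balance, restated.**

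| Expected benefit | NNT | Benefit : harm at 10% (as printed) | Benefit : harm at 20% (endpoint) |
|---|---|---|---|
| Dose reduction, 60% | 1/0.60 = 1.7 | 6 : 1 | 3 : 1 |
| Stopping, 15% | 1/0.15 = 6.7 | 1.5 : 1 | 0.75 : 1 |

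For stopping the balance reverses; for dose reduction it is halved but still favours the strategy. The printed NNTs of 1.5 and 6 are loose roundings of approximate percentages and do not affect this.

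**5. The same mixing in the planning rate.** The 15% for usual care is a rate of biologic change. It enters the calculation as a rate of persistent flare, without the discount that the margin paragraph applies to patients who switch. The 5% added for the intervention arm is already described as persistent flare after failed reinstatement. So the section moves between flares that lead to a switch and flares that persist.

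**The case against.** **A late switch.** Under Interventions, a confirmed flare in the dose-reduction arm first leads back to the last effective interval, and a switch is advised only if the original regimen also fails. Confirmation takes at least 4 weeks and regular visits are three-monthly. Some patients could pass three months, and so count as events, before they switch; half might then respond, and NNH 10 would describe the remainder. This part stands: a reader might infer that the endpoint has already removed every patient who responds to a switch, and the documents do not establish that. It does not rescue the figure. Each of the 20% would still be a primary-outcome event, and the margin paragraph itself calls the remaining half the persistent flares.

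**The decision rule is stated consistently.** Correct. A reader might infer that the margin ought to be 10 points or that the trial is too small. The documents support neither: the 20 points is applied openly and throughout, and the sample size follows from it.

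**35% is only the boundary.** Also correct. A true excess at the margin would pass about 5% of the time, and the planned excess is 5 points (NNH 20). With 15% observed in control and 57 and 114 patients, a one-sided 95% Wald upper limit below 20 points needs an observed excess of about 9.8 points or less. But that is a point estimate. A margin is judged by the excess that a passing result excludes, and NNH 10 is the authors' figure for that limit.

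**Conclusion.** Wrong as written, and should be fixed. On persistent flare as defined, the margin corresponds to an NNH of 5, not 10. At that limit harm (20%) exceeds the expected share who stop the drug (15%) but stays well below the expected share who reduce the dose (60%), so the authors' broader view that more patients gain than are harmed can still hold for dose reduction.

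This rests on the endpoint definition under Outcome measures and on the authors' own 60% and 15%. It does not depend on how early patients switch. The fault is confined to the justification: the hypotheses, sample size and formal threshold stand.

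**What to change.** - Keep 20 points as the formal margin. Remove the halving step and state that the margin equals an NNH of 5 on persistent flare, set against NNTs of about 1.7 and 6.7.
- If NNH 10 is meant for patients who still do not respond after a later switch, name that as a different outcome.
- Reconcile the flare definition under Outcome measures with both Sample size paragraphs, including the use of a biologic-change rate as the persistent-flare rate.
- Report the confidence interval for the difference in persistent flare and say whether it also excludes a 10-point excess, the harm the authors said they accept. If it does not, limit the claim to having excluded an excess above 20 points. Planned data analysis names Fisher exact testing for this comparison, so the interval should be named alongside it unless the full analysis plan already does so.

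The cost is a few sentences and one further reading of an interval that a non-inferiority report needs anyway. No data collection changes. The downside is a less favourable stated harm figure.
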